## Abstract

**Background:**

Herpes zoster (HZ), triggered by the reactivation of the varicella-zoster virus, manifests as a painful rash known as zoster-associated pain (ZAP), which can progress to postherpetic neuralgia (PHN). This study evaluates the efficacy and safety of ultrasound-guided thoracic paravertebral injections of platelet-rich plasma (PRP) in managing acute ZAP and preventing PHN.

**Methods:**

This is a prospective, randomized, controlled, open-label, endpoint-blinded, single-center trial involving 128 participants suffering from zoster-associated pain. Participants will be randomly assigned to the PRP treatment in combination with antiviral therapy group or the antiviral therapy group at a 1:1 ratio. Pain intensity (NRS-11), quality of life (SF-12), sleep quality (PSQI), pain characteristics, skin lesion recovery, average weekly consumption of rescue analgesics, and adverse events will be assessed. Follow-up assessments will be conducted at 1, 3, 6, and 12 months post-intervention to evaluate the incidence rate of PHN, pain intensity, quality of life, sleep quality, and safety.

**Ethics and Dissemination:**

Adhering to the 2013 SPIRIT statement and the Declaration of Helsinki, this study has received ethical approval from the relevant committee. Results will be disseminated through scientific journals and conferences, contributing to global data on managing ZAP.

**Conclusions:**

By comparing PRP with antiviral therapy, this trial seeks to establish a more effective treatment paradigm for reducing acute zoster-associated pain and the incidence of PHN, potentially setting a new standard in therapeutic strategies for HZ.

**Trial Registration:**

This clinical trial is registered with the Chinese Clinical Trial Registry (ChiCTR) at https://www.chictr.org.cn/index.html (Registration Number: ChiCTR2400087248, Registration Date: 2024–07-23).

## Key Summary Points

**Table Taba:** 

***What did the study ask?***
This study aims to assess the effectiveness and safety of platelet-rich plasma (PRP) injections, comparing it with standard antiviral therapy to reduce zoster-associated pain (ZAP) and prevent postherpetic neuralgia (PHN).
***What was learned from the study?***
Expected outcomes include insights into the impact of PRP on managing acute ZAP and potentially establishing PRP as an effective adjunctive therapy to antiviral treatments in preventing PHN.
The study may pave the way for new treatment strategies in herpes zoster (HZ)-related pain management, especially if PRP is shown to improve long-term outcomes.

## Background

Herpes zoster (HZ), commonly known as shingles, is a painful dermatological condition triggered by the reactivation of the varicella-zoster virus (VZV). Approximately 30% of individuals are at risk of developing HZ over their lifetime if not vaccinated [1]. This virus resides in a dormant state within the dorsal root or trigeminal ganglia in adults. Its reactivation induces acute neuroinflammation and subsequent long-term damage to neurons and supportive cells, resulting in persistent pain known as zoster-associated pain (ZAP). Postherpetic neuralgia (PHN) is conventionally defined as pain in the affected dermatome that persists for at least 3 months after the healing of the acute herpes zoster rash [2]. Patients over the age of 50 are more likely to develop HZ [3, 4]. PHN can significantly impact patients' quality of life, causing persistent pain that interferes with daily activities and sleep.

Antiviral treatment is the cornerstone of HZ management, aiming to reduce viral replication, accelerate lesion healing, and alleviate acute pain. Common antiviral agents include acyclovir, valacyclovir, and famciclovir, which inhibit viral DNA synthesis. Despite their efficacy in reducing acute pain and viral shedding, antiviral medications have limitations. They do not completely prevent the development of PHN, particularly in patients with severe initial pain, older age, combined with underlying diseases or compromised immune systems [5, 6]. The partial efficacy of antivirals underscores the need for adjunctive therapies to more effectively manage ZAP and prevent its progression to PHN [7]. Studies highlight the thoracic region as the most commonly affected area [8].

Platelet-rich plasma (PRP) is a preparation made by extracting and enriching platelets from the patient's own blood. PRP contains high concentrations of growth factors and cytokines, which promote tissue repair, angiogenesis, and anti-inflammatory effects. The mechanisms of PRP include the release of bioactive molecules such as platelet-derived growth factor (PDGF), transforming growth factor-beta (TGF-β), and vascular endothelial growth factor (VEGF), which enhance tissue healing and reduce inflammation. Recent advances suggest that PRP can improve outcomes in various medical conditions, including chronic wounds, musculoskeletal injuries, and dermatological disorders [9–11]. PRP has been demonstrated to possess nerve repair and pain relief properties and has been studied in the treatment of both peripheral and central nervous system injuries, including the facial nerve [12–14], median nerve [15, 16], sciatic nerve [17, 18], and spinal cord [19, 20]. Although there is limited direct evidence supporting PRP’s role in preventing PHN, its regenerative and anti-inflammatory properties indicate its potential in managing ZAP and reducing the risk of PHN.

Given the limitations of current treatments and the potential benefits of PRP, our study aims to evaluate the additional effectiveness of PRP combined with standard antiviral therapy compared to antiviral treatment. To date, no comprehensive, long-term follow-up studies have evaluated the effect of PRP on ZAP. Therefore, a prospective, randomized study is needed to compare the effects of PRP on ZAP management and the prevention of PHN. This could provide a simple and feasible strategy for controlling ZAP and preventing PHN. Cadaver studies have demonstrated that under ultrasound guidance, thoracic paravertebral intervertebral injections encompassed the thoracic nerve root, reached the intervertebral foramen, and a spread is observed within the intercostal space, saturating the intercostal nerve [21–23]. Therefore, our research has decided to select ultrasound-guided thoracic paravertebral nerve injection technique as our fundamental technique for this study, comparing PRP injection therapy (experimental group) with antiviral therapy alone (control group).

## Methods

### Study Objectives

The primary objective of this study is to assess the effectiveness of ultrasound-guided thoracic paravertebral PRP injections in alleviating acute ZAP and preventing the onset of PHN. The secondary objective is to compare the outcomes of PRP injections with traditional antiviral therapy in treating acute HZ.

### Study Design and Recruitment

This study is a prospective, randomized, controlled, open-label, endpoint-blinded single-center trial. We plan to recruit 128 patients with ZAP at the Second Affiliated Hospital of Guangxi Medical University. Before the start of the study, all researchers will receive standardized training, including trial content, treatment strategies, treatment methods, evaluation and quality control, etc., and pass the assessment. Patients will be randomly assigned to the thoracic paravertebral PRP injection group or the antiviral therapy group at a 1:1 ratio. Recruitment will be conducted by experienced attending physicians.

All potential study participants will be provided with a detailed understanding of the study purpose, interventions, potential benefits, possible risks, and countermeasures, and will have at least 1 h to consider whether to join the study. They will be rigorously evaluated according to the inclusion and exclusion criteria. Eligible patients will be enrolled in the study and sign an informed consent form, with the right to withdraw from this study at any time. The confidentiality of participant records will be protected. The patient flow diagram of the clinical trial is illustrated in Fig. 1

**Fig. 1 Fig1:**
[figure not shown]
Trial flow diagram. *PRP* platelet-rich plasma

#### Inclusion Criteria

Diagnosed with HZ involving unilateral thoracic nerves (T1–T12).Age ≥ 50 years and disease duration ≤ 2 weeks.Average pain intensity score (11-point NRS) within 24 h before randomization ≥ 4 points.Agree to participate in this study and be able to sign the informed consent form.

#### Exclusion Criteria

Patients with disseminated HZ or combined with HZ at other locations.Coagulation dysfunction, taking anticoagulant drugs or/and antiplatelet drugs.Systemic infections or infection at the puncture site.Pregnant or lactating women.Patients with immunodeficiency diseases, severe cardiovascular, cerebrovascular, and respiratory diseases, or other serious systemic diseases that prevent cooperation with the treatment.Patients with psychiatric conditions.Patients with thoracic spine deformity or a history of thoracic spine surgery that affects ultrasound positioning.Patients who have contraindications for PRP or are allergic to treatment-related drugs such as famciclovir, gabapentin, pregabalin, nonsteroidal anti-inflammatory drugs (NSAIDs), and tramadol.Patients with a recent history of other pain management treatments

### Case Dropout Instructions

If a subject develops other comorbidities, complications, or special physiological changes during the trial and is deemed unfit to continue, they will be classified as a case dropout.If a subject encounters a serious or key adverse event during the trial, and our research team judges it inappropriate to continue, the subject will be withdrawn.If a subject adds medications not specified in the protocol or receives external treatment, it will be considered a protocol violation, and they must be removed from the trial.Subjects may choose to withdraw due to personal reasons or be lost to follow-up in the final stage of the trial.

For all cases of dropout, our research team will actively complete the last follow-up and examination to collect data and analyze effectiveness and safety. Detailed information on all dropout cases, including test results and reasons for dropout, will be fully documented on the case report form.

### Randomization and Blinding

Participants will be randomly assigned to receive either PRP treatment in combination with antiviral therapy or antiviral therapy alone in a 1:1 ratio using block randomization with a block size of 4, created with IBM SPSS Statistics 25.0. This sequence will be secured in numbered, opaque envelopes to ensure allocation concealment. Treatment efficacy and safety evaluations will be conducted by independent assessors unaware of the group assignments.

Due to the nature of the interventions, complete blinding is not possible for the doctors and patients. Therefore, this study will use blinded endpoints. The efficacy and safety evaluations will be performed by personnel not directly involved in the treatment. The evaluators who perform the assessments and the personnel conducting the statistical analysis will be blinded to the group assignments.

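### A single, published block size of 4 in an open-label, single-centre trial means that envelopes alone cannot guarantee allocation concealment

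*Protocol article*

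**What the plan says.** Under Randomization and Blinding, the protocol article allocates patients "in a 1:1 ratio using block randomization with a block size of 4, created with IBM SPSS Statistics 25.0". It then states: "This sequence will be secured in numbered, opaque envelopes to ensure allocation concealment". The same section concedes that "complete blinding is not possible for the doctors and patients" and relies on blinded assessors and blinded statistical staff.

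Under Study Design and Recruitment, the design is given as follows: "This study is a prospective, randomized, controlled, open-label, endpoint-blinded single-center trial". On who enrols patients: "Recruitment will be conducted by experienced attending physicians". Before the trial starts, "all researchers will receive standardized training, including trial content, treatment strategies, treatment methods" and more.

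The treatment sections make the arms easy to tell apart. Both receive oral famciclovir, and only the experimental arm also has four weekly ultrasound-guided injections.

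**The concern.** Concealment has two parts: the next slip must be unreadable, and it must not be deducible. Opaque envelopes serve the first part only. With one fixed block size, the second part depends on recruiters not knowing that size or not following the earlier allocations. The size is now in print, and in an open-label, single-centre trial earlier allocations are visible in practice to staff who care for the patients.

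If a recruiter does foresee the next arm, enrolment leaves room for judgement. The entry pain score is self-reported with a threshold of 4, some exclusions (serious systemic disease, recent other pain treatment) call for interpretation, and consent is led by physicians. The Background names severe initial pain, older age and underlying disease as features of patients in whom antivirals do not fully prevent postherpetic neuralgia (PHN), and a recruiter can see all of these. Selective enrolment would bias the comparison of PHN incidence. Blinding of assessors and statisticians would not prevent this, because it acts after allocation.

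**Working it through.** **Inputs from the protocol article.** Block size 4 and ratio 1:1 (Randomization and Blinding). Total 128, or 64 per arm (Sample Size Calculation), which is 128 / 4 = 32 blocks. The article gives no predictability figure to reproduce. The total is used only to count blocks, and it follows from the article's own figures: 58 × 1.10 = 63.8, rounded up to 64 per arm.

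**Assumptions.** One unstratified sequence, since no strata are mentioned. The observer knows the block size, knows where blocks begin and follows every allocation in order.

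**Certain predictions.** A balanced block of 4 has 4! / (2! × 2!) = 6 equally likely sequences.
- Positions 1 and 2 are never determined.
- Position 3 is determined when the first two allocations match: 2 of 6 sequences, probability 1/3.
- Position 4 is always determined.

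The expected number per block is 1/3 + 1 = 1.333, and 1.333 / 4 = 33.3%. Over the trial this is 32 × 1.333 = 42.7, about 43 of 128. Each block yields either 1 or 2 determined positions, so the total lies between 32 and 64, with SD √(32 × 1/3 × 2/3) = 2.7.

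**Best guess (always name the arm that is behind in the block).**
- Position 1: 1/2.
- Position 2: 2/3, since 2 of the 3 remaining slips are for the other arm.
- Position 3: (1/3 × 1) + (2/3 × 1/2) = 2/3.
- Position 4: 1.

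The sum is 17/6 = 2.833 per block, and 2.833 / 4 = 17/24 = 70.8%, or 90.7 of 128. With no information the rate is 50%.

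**Alternatives.** Fixed blocks of 6 and 8 were enumerated in the same way. Random block sizes were simulated (400 lists of 128) for an observer who knows the possible sizes and all past allocations, but not the order of the sizes.

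| Block scheme | Certain predictions | Best guess correct |
|---|---|---|
| Fixed 4 (as planned) | 33.3% | 70.8% |
| Fixed 6 | 25.0% | 68.3% |
| Fixed 8 | 20.0% | 66.6% |
| Random 4 and 6 | about 5% | about 69% |
| Random 4, 6 and 8 | about 2% | about 68% |

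Varying the sizes removes nearly all certain predictions but only dents the best-guess rate.

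**The case against.** The strongest reply is that the figures describe an ideal observer. The article says that doctors cannot be blinded. It does not say that recruiters also treat, that any one of several attending physicians sees the ordered sequence, or who holds and opens the envelopes. A condensed article commonly leaves out custody of the list, so that silence is no fault. This stands: the 33% and 71% are upper bounds.

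A reader might also infer that any resulting bias could not be repaired. The documents do not support that in full. Baseline pain score and demographics are collected at enrolment (Table 1), so imbalance in pain or age would be visible and could be adjusted for. The article's primary comparison is a chi-square test with a relative risk, so adjustment would be an additional analysis, and it would not reach selection on unmeasured factors.

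Room for manoeuvre is also limited. Disease duration must be at most 2 weeks, and 128 patients over about 3 years is one every 3 × 365 / 128 = 8.6 days, so holding a patient back for a later slot is hard. Declining or encouraging a patient remains possible.

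Finally, the protocol already places screening, consent and a pain score ahead of allocation (Inclusion Criteria, Table 1). That safeguard is sound, but it does not stop a recruiter who can anticipate the arm from choosing whom to put forward.

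**Conclusion.** The point holds in conditional form. The fixed block of 4 is a positive and published choice, not a detail left to another document, and with it the statement that envelopes ensure concealment goes too far. Up to one third of allocations on average (about 43 of 128) could be deduced with certainty, and 71% guessed correctly, by someone who knows the block size and follows the sequence.

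The arithmetic is exact for a single unstratified list. If undescribed strata exist, the same fraction applies to completed blocks within each stratum, though tracking would be harder. It would be wrong to read this as showing that recruiters know every past allocation, or that selection bias has occurred or will occur. The documents establish neither. This is an avoidable weakness worth mending, and it does not invalidate the design.

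**What to change.** For patients not yet randomised, regenerate the remaining list with randomly varying block sizes, for example 4, 6 and 8. Do not disclose the sizes to recruiting staff, and have the list held by someone outside recruitment. The independent holder matters as much as the varied sizes, because varied sizes alone leave a best-guess rate of about 68–69% for an observer who follows all allocations. Soften the statement that envelopes ensure concealment. No new rule is needed for recording eligibility and the baseline pain score before allocation, since the protocol already orders these steps.

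Costs: a new list and envelopes for the unused part, and possibly a protocol amendment, because the method belongs to an approved and registered plan. The possible imbalance at the end is slightly larger. The largest difference between arms inside a block is half its size, so stopping mid-block could leave a difference of up to 8 / 2 = 4 patients, against 4 / 2 = 2 now (and 0 if exactly 32 blocks of 4 are filled). Patients already randomised and the sample size are unaffected.

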### Interventions

#### PRP Preparation

In this study, we employed a classical two-step centrifugation method to prepare 3 ml of PRP for paravertebral injection therapy. The PRP used in this study is classified as pure PRP (P-PRP), which contains a high concentration of platelets but minimal leukocytes, following the classification by Dohan Ehrenfest et al.[24].Blood collection: Approximately 30 ml of venous blood is drawn from each patient using sodium citrate as an anticoagulant to inhibit coagulation.First centrifugation: The collected blood undergoes a first centrifugation at room temperature at low speed (160–200 g) for 15 min, resulting in a separation into three distinct layers: a lower red blood cell layer, a middle buffy coat rich in white blood cells, and an upper plasma layer with a low platelet count.Platelet enrichment: The upper layer of plasma, excluding the white blood cell-rich buffy coat, is gently transferred to a new sterile centrifuge tube, taking care to avoid disturbing the middle layer.Second centrifugation: This plasma is then centrifuged at a higher speed (500–600 g) for 10 min to further concentrate platelets at the bottom of the tube.PRP collection: After centrifugation, the upper plasma is carefully aspirated, leaving about 4 ml of PRP at the bottom of the tube. From this, 1 ml is used for platelet counting and activity analysis to ensure the prepared PRP meets clinical standards, and the remaining 3 ml is utilized for ultrasound-guided paravertebral injections.

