#### Ultrasound-Guided Thoracic Paravertebral Injection Technique

We adopted an ultrasound-guided approach for thoracic paravertebral injection, as detailed in Pu et al. [25]. The patient will be placed in the prone position to optimize access to the thoracic paravertebral space. A low-frequency convex array ultrasound probe (2–5 MHz) will be used to localize the target thoracic levels, starting in the paraspinal sagittal position and moving caudally to identify the ribs. After identifying the first rib, the probe will be moved further down the thoracic spine to locate the target segments. Typically, one to three thoracic levels will be selected based on the dermatomal distribution of ZAP, with emphasis on the most affected segments (e.g., T3, T4, and T5 for T3–T5 involvement).

Once the target level is identified, the probe will be rotated 90 degrees to achieve an axial view, allowing visualization of the transverse process, inferior articular process (IAP), and parietal pleura (PP). A 22-gauge, 80–100-mm echogenic needle will be inserted in-plane from lateral to medial, aiming for the midpoint between the IAP and PP. Doppler ultrasound will be used to avoid puncturing vascular structures. After confirming the needle placement, 3 ml of PRP will be injected at each targeted level under continuous ultrasound guidance.

Following the injection, patients will be monitored for 30 min to observe any adverse effects. A follow-up ultrasound will be performed to verify the distribution of the injectate and exclude complications such as hematomas or pleural punctures.

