#### Treatment Interval and Treatment Dose

Patients in both groups will receive standard antiviral therapy with famciclovir 500 mg 3 times daily for 7 days, initiated immediately upon recruitment during the viral outbreak [26]. In addition to the standard antiviral therapy, patients in the experimental group will receive PRP injections. The interval between each ultrasound-guided thoracic paravertebral injection is one week, with a total of four injection treatments. Each injection includes 3 ml of PRP per affected thoracic nerve.

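### The preparation section leaves 3 ml of PRP for injection, but the technique and dose sections call for 3 ml at each of one to three levels, so the figures agree only for single-level patients

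*Protocol article*

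**What the plan says.** Three neighbouring sections under Interventions in the protocol article give volumes.

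- **PRP Preparation.** The stated aim fixes the yield: "we employed a classical two-step centrifugation method to prepare 3 ml of PRP for paravertebral injection therapy". The steps then give the quantities: "Approximately 30 ml of venous blood is drawn from each patient using sodium citrate as an anticoagulant to inhibit coagulation"; after the second spin the upper plasma is drawn off, "leaving about 4 ml of PRP at the bottom of the tube"; of this, "1 ml is used for platelet counting and activity analysis", and "the remaining 3 ml is utilized for ultrasound-guided paravertebral injections". The section does not say how often the preparation is carried out.
- **Ultrasound-Guided Thoracic Paravertebral Injection Technique.** "Typically, one to three thoracic levels will be selected based on the dermatomal distribution of ZAP". The section illustrates this with a three-level case (T3, T4 and T5). Then: "3 ml of PRP will be injected at each targeted level under continuous ultrasound guidance".
- **Treatment Interval and Treatment Dose.** There are four treatments, one week apart. "Each injection includes 3 ml of PRP per affected thoracic nerve".

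No section ties the blood draw or the number of preparations to the number of levels, and none divides the 3 ml between levels.

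**The concern.** The first section states a supply and the other two state a demand. The supply is a fixed volume, while the demand rises with the number of levels treated. They can match at only one number of levels, although the article treats up to three as typical.

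This matters because PRP injection is the experimental treatment. An operator facing a two- or three-level patient has to settle the conflict alone, for example by dividing the volume or by preparing more. Different operators may settle it differently, and the choice arises only in patients with more than one level. The treatment actually tested could then vary with disease extent and with operator, and the trial report could not say plainly what volume was given.

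A second consequence is possible but conditional. The Additional Intervention section treats a PRP course that is not completed, whatever the reason, as a protocol violation leading to exclusion. If a volume shortfall were handled that way, the resulting exclusions could fall only on the PRP arm, because the control arm has no injections.

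**Working it through.** **Inputs, all from the protocol article**

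- PRP left after the second spin: about 4 ml (PRP Preparation)
- PRP used for testing: 1 ml (PRP Preparation)
- Volume per level or affected nerve: 3 ml (technique and dose sections)
- Levels treated, L: typically 1 to 3 (technique section)
- Treatments: 4, one week apart (dose section)

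**Assumption:** one preparation per session. The article gives no frequency.

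**Step 1: reproduce the plan's own figure.** Available = 4 − 1 = 3 ml. This matches the stated 3 ml, so the subtraction itself is correct.

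**Step 2: compare supply and demand.** Required per session = 3 × L ml. Shortfall = required − 3 ml. If a single 3 ml preparation were divided, each level would get 3 / L ml.

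| Levels (L) | Required per session | Available | Shortfall | Share covered | Per level if divided | Required over 4 sessions | Available over 4 sessions |
|---|---|---|---|---|---|---|---|
| 1 | 3 ml | 3 ml | 0 | 100% | 3.0 ml | 12 ml | 12 ml |
| 2 | 6 ml | 3 ml | 3 ml | 50% | 1.5 ml | 24 ml | 12 ml |
| 3 | 9 ml | 3 ml | 6 ml | 33% | 1.0 ml | 36 ml | 12 ml |

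**Step 3: vary the assumption about frequency.**

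- One preparation per patient: 3 ml in total against 12, 24 or 36 ml. The conflict is larger and reaches single-level patients too.
- One preparation per session: as in the table.
- One preparation per level per session: supply equals demand. The article does not state this, and it describes the blood draw by patient.

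**Step 4: does the sample size depend on this?** No. With 34.8% against 10%, a two-sided 5% level and the stated 90% read as power, the usual two-proportion formula gives 58 per group, as the Sample Size Calculation section states. Injected volume does not enter it.

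The figures show the size of the disagreement only. They do not indicate which volume is right.

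**The case against.** The strongest defence is that the preparation section describes a unit batch. Its 3 ml equals the per-level volume in the other two sections, and those two agree with each other. On that reading the batch is repeated for as many levels as needed, and a condensed article leaves the scaling to the full protocol. Part of this stands: the volume per level is stated consistently, the frequency of preparation is unstated, and repetition is not ruled out. But the article nowhere says that batches are repeated. It draws the blood by patient, and it assigns the remaining 3 ml to injections in the plural. The point is a conflict between volumes that are stated, so it is not an omission that a fuller document would naturally fill.

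Several stronger readings are tempting and go beyond the text.

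- **That multi-level patients cannot be treated at all.** This does not follow. An operator could divide the volume or prepare more. What is shown is that the sections cannot all be followed literally under one preparation per session.
- **That patients with wider disease will be lost selectively from the PRP arm.** The exclusion rule in Additional Intervention does not mention volume, and an operator who improvises still completes the session. The plan also promises both intention-to-treat and per-protocol analyses, and a last follow-up for dropouts. These do not remove the tension with the exclusion rule, but selective loss remains a possibility and is not a finding.
- **That a larger volume would mean a specific loss of platelet concentration or a specific extra blood draw.** The article gives no platelet recovery rate, no target concentration and no rule on pooling batches, so such figures would rest on assumptions from outside it.
- **That the low platelet count ascribed to the plasma layer after the first spin contradicts the high concentration of the product.** The first describes an intermediate layer and the second a product that has been spun again. The article alone does not show an error.

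**Conclusion.** The concern holds as an internal inconsistency between the preparation section and the technique and dose sections. It is not an arithmetic error: the subtraction that yields 3 ml is right.

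Assuming one preparation per session, the stated supply covers all of the stated volume for one level, half for two levels and a third for three. Single-level patients are unaffected on that assumption. The article does not give the share of multi-level patients, so the number of participants concerned cannot be computed.

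The definition of the primary outcome, its test and the sample size are untouched. What is at risk is the uniformity of the experimental treatment and the ability to report what was delivered. Any effect on who remains in the PRP arm depends on how a shortfall is handled. The point is worth correcting because it concerns the treatment under test and is cheap to settle. It is not grounds for holding the design to be unworkable.

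**What to change.** Reconcile the sections PRP Preparation, Ultrasound-Guided Thoracic Paravertebral Injection Technique, and Treatment Interval and Treatment Dose. Blood drawn, number of preparations, PRP produced and volume per level should agree for one, two and three levels, and the frequency of preparation should be stated. Which figures stand is for the clinical team to decide; this review takes no view on it.

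Record the levels treated and the volume given at each level at every session, so that the delivered treatment can be described in the report. Leaving this out of an article is not itself a fault, but the record is needed while the volumes are in doubt.

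The cost is a protocol clarification, an instruction to operators and, if not already collected, two items on the case report form. Ethics notification would be needed if the blood volume changes. The sample size and the planned analyses stay as they are.
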